##### Moca

The Montreal Cognitive Assessment will be used to screen for mild cognitive dysfunction at baseline (T0). The test assesses eight domains of cognitive functioning: attention and concentration, executive functions, memory, language, visuoconstructional skills, conceptual thinking, calculations, and orientation [44].

#### Quality of life

##### EQ-5D-5L

The 5-item, 5-level EuroQoL is used to monitor changes in health-related quality of life (in terms of quality-adjusted life years, QALYs) and is completed at T0 and follow-up (T2, T3 and T4) [31, 50].

##### WHODAS 2.0

The World Health Organization disability assessment schedule evaluates the degree of disability based on the ICIDH-2 model of health-related states and functioning. The WHODAS 2.0 determines disability associated with both physical and mental disorders in both general and clinical populations [13]. Recently, an algorithm has been developed to map WHODAS 2.0 scores on disability weights [37]. The WHODAS is administered at all five assessment timepoints.

#### Economic evaluation

##### TiC-P

The Netherlands Institute of Mental Health and Addiction and iMTA Cost Questionnaire for Psychiatry [26] will be administered to assess healthcare utilization, patients’ out-of-pocket costs and productivity losses stemming from absenteeism and lesser productivity when working. The TiC-P is the most frequently used health service receipt questionnaire in the Netherlands. It will be administered at T0 and follow-up (T2, T3, and T4).

### Implementation study

Alongside the RCT, we will conduct a quantitative and qualitative implementation study. The overall goal of the implementation study is to examine acceptability and feasibility of CCT and to identify facilitating and impeding factors in the implementation process. It contains three parts, each part addressing a separate target group:Participants: we will conduct qualitative in-depth interviews in different subsamples of patients (responder/non-responders; drop-out/no drop-out). We aim for 16 to 20 interviews, or until data saturation has been reached. Topics are partly guided by items of the Patient Education Materials Assessment Tool for Audiovisual Materials [55] and will address satisfaction, experienced effects, usability, understandability, support, and clarity of the intervention. Interviews will take place between T2 and T3. In addition, two questions on satisfaction are added to the T1 RCT questionnaire for participants in the experimental group, and the research team will systematically assess the reasons for potential drop-out.Healthcare professionals: the perceptions of the health care professionals (therapists and coordinating professionals in the teams) will be evaluated by conducting a focus group with a subsample of 6 to 8 of them. Topics will include satisfaction, appropriateness, embedding in work routine, acceptability, and facilitating and impeding factors for current and eventual future implementation of CCT in mental healthcare. These topics are based on a review that identified the most important factors that can promote or inhibit implementation of online interventions for mood disorders in routine practice [61]. The focus group will take place at the end of the inclusion phase. Moreover, all healthcare professionals involved will receive an online survey, containing the same topics as in the focus group, as well as the Normalization MeAsure Development (NoMAD) questionnaire: a 20-item self-report instrument based on Normalization Process Theory that measures implementation processes [38, 62].Stakeholders: if the RCT shows (cost-)effective results, we will conduct a focus group interview with all stakeholders in order to identify facilitators and barriers for nationwide implementation. Stakeholders are, again, representatives from the patients and health care professionals, as well as representatives from the Netherlands Ministry of Health, Welfare and Sport, insurance companies, Netherlands Healthcare Authority and the Committee for clinical guidelines in depression treatment. These final results of the implementation study will be summarized in an implementation plan for future rollout.

The implementation study takes place in an iterative process whereby new insights can lead to adjustments in order to ensure optimal inclusion and implementation during the trial.

### Statistical analyses

#### Sample size calculation

A previous power calculation based on MDD studies demonstrated that an effect size of η^2^ = 0.11 or larger should be attainable [35]. This is equivalent to a standardized mean difference of Cohen’s d = 0.70 or larger. In the current study protocol, which is powered based on the expected effect on the primary outcome measure, we prefer to make a more conservative assumption regarding the expected effect size and opt for d = 0.45, corresponding to a medium-size effect, which would be relevant from a clinical point of view. Effects of d = 0.45 (if present) will be statistically significant in a baseline adjusted ANCOVA with one baseline (post-training) and four follow-ups (at 3, 6, and 12 months) at α = 0.05 (2-tailed) and a power of (1-ß) = 0.80. Assuming a correlation of *r* = 0.50 between baseline and first follow-up and again *r* = 0.50 between subsequent follow-ups, we need *n* = 33 per condition to attain a well-powered study.

However, we will also take into account that the data of the participants will be ‘clustered’ within treating clinicians, which introduces a design effect of de = 1.56 when the mean cluster size is m = 10, the coefficient of variation is cv = 0.475, and the intraclass correlation icc = 0.05 [21]. Multiplying the sample size (*n* = 33 per condition) × the design effect de = 1.56 indicates that, at baseline, we need *n* = 52 per condition or *n* = 104 for both arms. We will not compensate for loss to follow-up because we will conduct intention-to-treat analyses (i.e., including all participants as randomized) as per the CONSORT statement – either using (generalized) mixed models or multiple imputation of missing observations.

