#### Depressive symptoms

##### Ids-SR

The Dutch version of the Inventory of Depressive Symptomatology Self Report [52] will be used to assess the severity of depressive symptoms. It consists of 30 items covering various symptom domains of depression. Apart from the baseline measurement (T0), the questionnaire will be administered within 1 month after CCT completion (T1) to measure the direct effects of CCT, and at three follow-up timepoints (T2, T3, and T4) to evaluate the longer-term effects (up to 12 months). Treatment response will be defined as a 50% IDS-SR symptom reduction between baseline and 12-month follow-up. Depression remission will be defined as an IDS-SR score of ≤14.

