#### Evaluation of clinical outcomes

All analyses will be conducted in agreement with the intention-to-treat (ITT) principle as per the CONSORT statement [40]. We will repeat the analyses in the per-protocol sample: participants who completed at least six training sessions. We will use two-level generalized mixed models on the longitudinal dataset to analyze the clinical outcomes over all 4 time points with condition, time and the interaction of condition x time as factors and the depended baseline measure as covariate while accounting for the multilevel data structure with participants being ‘nested’ in clinicians and assessments ‘nested’ within participants [27]. We will examine baseline cognitive control, depression severity, and age as possible moderators. We will examine the latter as possible moderating variable, because age was a relevant correlate for the effect of the aPASAT on depressive symptoms [12]. Rumination and working-memory functioning will be evaluated as potential mediators of change in depressive symptoms, for which Hayes’ PROCESS macro (in SPSS) will be used. These evaluations of the clinical outcomes will be carried out in SPSS [30] and Stata [58].

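### The sample-size statement mislabels the baseline and miscounts the follow-ups, and its n = 33 per arm at 80% power fits three follow-ups, not the four outcome visits that will be analysed

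*Protocol article*

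**What the plan says.** Under Sample size calculation, the protocol describes the powered model as a "baseline adjusted ANCOVA with one baseline (post-training) and four follow-ups (at 3, 6, and 12 months"). The other inputs in that section are:

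- Effect size: the authors "opt for d = 0.45, corresponding to a medium-size effect".
- Error rates: "at α = 0.05 (2-tailed) and a power of (1-ß) = 0.80".
- Correlations: "Assuming a correlation of *r* = 0.50 between baseline and first follow-up and again *r* = 0.50 between subsequent follow-ups".
- Clustering by clinician: a "design effect of de = 1.56 when the mean cluster size is m = 10, the coefficient of variation is cv = 0.475", with an intraclass correlation of 0.05.

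The result is 33 per condition before clustering and 52 after it: "per condition or *n* = 104 for both arms". Nothing is added for loss to follow-up.

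Other sections describe the visits differently. On the primary measure, the Ids-SR section says: "Apart from the baseline measurement (T0), the questionnaire will be administered within 1 month after CCT completion (T1"), followed by three later assessments. Aims and hypotheses counts T1 among the visits at which outcomes are assessed, together with T2, T3 and T4. Table 1 shows the IDS-SR at all five visits, with T0 as the baseline column. Evaluation of clinical outcomes then specifies a mixed model "over all 4 time points with condition, time and the interaction of condition x time as factors and the depended baseline measure as covariate".

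**The concern.** The sentence that justifies the trial's size disagrees with itself and with the rest of the protocol. It attaches the word baseline to a visit that takes place after randomisation and training. It also gives a count of four beside a list of three.

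This could be a slip of punctuation, with the post-training visit belonging inside the second bracket as the first of four follow-ups. If so, the stated number should come out of the stated inputs with four follow-ups, and it does not. If instead the list of three is what was used, the number comes out, but for a model with one outcome visit fewer than the planned one. On either reading, a reader cannot get from the described model to 33 per arm at 80% power, and 33 is what 52 per arm and 104 in total are built on.

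**Working it through.** **Inputs** (all from Sample size calculation): d = 0.45 in SD units, two-sided α = 0.05, power 0.80, r = 0.50, cluster size m = 10, cv = 0.475, icc = 0.05.

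**Formula.** For the mean of k follow-ups adjusted for one baseline, with all correlations equal to r, the variance factor is f = (1 + (k − 1)r)/k − r². The number per arm is n = 2(1.960 + 0.8416)² f / d². Here 2 × 2.8016² / 0.45² = 77.52, so n = 77.52 f.

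**Step 1: reproduce the plan's figure.**

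- k = 3: f = (1 + 1.0)/3 − 0.25 = 0.4167, and n = 77.52 × 0.4167 = 32.30, so 33. This matches.
- Design effect: 1 + ((1 + 0.475²) × 10 − 1) × 0.05 = 1.563. This matches 1.56.
- 33 × 1.56 = 51.48, so 52 per arm and 104 in total. This matches.

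**Step 2: the four visits of the planned analysis, same inputs.**

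- k = 4: f = (1 + 1.5)/4 − 0.25 = 0.375, and n = 77.52 × 0.375 = 29.07, so 30.
- 30 × 1.56 = 46.8, so 47 per arm and 94 in total.
- With a t correction the figures are 34 (k = 3) and 31 (k = 4), so the difference of three per arm remains.

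**Step 3: the other reading of the correlations.** The text gives 0.50 from baseline to first follow-up and 0.50 between subsequent follow-ups. This could mean adjacent visits only, with correlations decaying as 0.50, 0.25, 0.125 and so on (AR(1)). Then f is the variance of the mean follow-up minus the square of its covariance with baseline.

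- k = 3: f = 0.6111 − 0.2917² = 0.526, and n = 40.8, so 41.
- k = 4: f = 0.5156 − 0.2344² = 0.4607, and n = 35.7, so 36. Then 36 × 1.56 = 56.2, so 57 per arm and 114 in total.

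Neither gives 33. Analysing follow-up means without baseline adjustment, with r = 0.50 throughout, gives 52 (k = 3) or 49 (k = 4); change scores give the same. Among two-sided calculations with three or four follow-ups, only baseline-adjusted ANCOVA with k = 3 and equal correlations returns 33.

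**Step 4: power at the planned size.** The effective number per arm is 52/1.56 = 33.3. Power is Φ(0.45/√(2f/33.3) − 1.960), for the average over visits with complete data.

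| Follow-ups | All r = 0.50 | AR(1), adjacent r = 0.50 |
|---|---|---|
| 3 | 81% | 72% |
| 4 | 85% | 77% |

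**The case against.** The strongest reply is that this is a misplaced bracket with no consequence. Evaluation of clinical outcomes uses four time points and a baseline covariate. Table 1 has five IDS-SR assessments, so T0 must be the covariate and T1 to T4 the outcomes. The analysis is therefore already settled. On equal correlations the planned model needs fewer participants than stated, so 104 remains sufficient on this ground.

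Most of that stands, and it rules out two stronger readings that a reader might infer. The first is that the calculation was run with T1 as covariate. The document does not show this: the formula uses only the number of follow-ups and the correlations, so 33 fits a T0 or a T1 baseline equally well. The second is that the trial will adjust for the post-training score and so remove the effect already present at T1. The analysis section and Table 1 point to T0, and no analysis passage makes T1 the covariate.

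The reply does not rescue the stated figure. Moving the bracket makes the wording consistent, but the inputs then give 30, not 33. The reassurance about 104 also depends on a correlation structure that the text leaves open.

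**Conclusion.** The point stands as a moderate one: a stated sample-size justification that does not match the planned model. The baseline is mislabelled, the count and the list of follow-ups disagree, and 33 per arm at 80% power is the answer for three follow-ups. For the planned four, the same inputs give 30 per arm, or about 85% power at 104 participants. On equal correlations the error is therefore conservative.

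That conclusion rests on three assumptions. First, all correlations are 0.50; if 0.50 holds only between adjacent visits, power at 104 is about 77% and 36 per arm would be needed before inflation. Second, data are complete and the plan's own design effect applies. Third, the effect of interest is the average over the four visits, which the model with its condition-by-time term does not single out.

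A reader might also infer that the trial can be reduced to 94 participants. The documents do not support this: no allowance is made for loss to follow-up, so the margin above 30 per arm is the only slack, and it disappears under decaying correlations.

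**What to change.** Reword the sentence to specify one baseline (T0) and four post-randomisation assessments (T1 post-training, and 3, 6 and 12 months post-training). Keep 104 participants. Restate the power for the four-visit average with complete data and the design effect of 1.56, and name the correlation structure: about 85% if all correlations are 0.50, and about 77% if 0.50 applies only to adjacent visits. Do not restate the requirement as 30 per arm.

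The cost is one sentence and one recalculated power statement. Recruitment, visits and the analysis model do not change.

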#### Evaluation of clinical outcomes

All analyses will be conducted in agreement with the intention-to-treat (ITT) principle as per the CONSORT statement [40]. We will repeat the analyses in the per-protocol sample: participants who completed at least six training sessions. We will use two-level generalized mixed models on the longitudinal dataset to analyze the clinical outcomes over all 4 time points with condition, time and the interaction of condition x time as factors and the depended baseline measure as covariate while accounting for the multilevel data structure with participants being ‘nested’ in clinicians and assessments ‘nested’ within participants [27]. We will examine baseline cognitive control, depression severity, and age as possible moderators. We will examine the latter as possible moderating variable, because age was a relevant correlate for the effect of the aPASAT on depressive symptoms [12]. Rumination and working-memory functioning will be evaluated as potential mediators of change in depressive symptoms, for which Hayes’ PROCESS macro (in SPSS) will be used. These evaluations of the clinical outcomes will be carried out in SPSS [30] and Stata [58].

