## Background

Late-life depression (LLD), defined as major depressive disorder in individuals over 60 years of age, is a severe psychiatric illness, and has a prevalence ranging between 1 and 16% [20]. LLD has a poor long-term prognosis, and is associated with chronicity and high mortality [32, 34, 39]. Research shows that relapse, recurrence, and chronicity are higher in LLD than they are in younger populations [25], while in later life longer duration and chronicity are associated with further cognitive decline and somatic comorbidity such as cerebrovascular diseases and diabetes [2, 15, 47]. Due to aging of the global population, the burden associated with LLD is expected to increase further, which underscores the necessity of appropriate, evidence-based, and cost-effective treatments that are tailored to older populations [9].

Older adults with depression seem less responsive to standard treatment protocols than their younger counterparts. The Netherlands Study of Depression in Older Persons (NESDO) reported that only 18% of their participants diagnosed with major depressive disorder (MDD) had recovered after 2 years [15], despite having received psychopharmacological and psychotherapeutic treatment from primary or specialized mental health-care services. In comparison, approximately 80% of a younger adult population recovered in a two-year period [57]. Moreover, the efficacy of antidepressant medication is lower in older adults than it is in younger adults, which is possibly related to age-related cognitive impairments [4, 49]. For example, a meta-analysis of 74 studies showed that the number needed to treat for antidepressants was six for adults, eight for persons over 55 years and 21 for people over 65 years [59]. Furthermore, for older depressed patients access to therapy is limited [16] and treatment often does not take into account underlying age-specific contributing factors. Arguably, add-on treatments aimed at distinct mechanisms of LLD may improve outcomes in this population.

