Impairment in a broad range of cognitive functions [51] is a common and disabling factor in LLD [42]. Apart from manifesting in performance tasks, cognitive deficits have also been observed in the brain. On a structural level, temporary changes in frontal brain regions are related to depressive symptomatology [1, 42] but particularly relevant are the changes discerned in the cognitive control network (CCN), which consists of the dorsolateral prefrontal cortex (DLPFC), the dorsal anterior cingulate cortex (dACC), and parietal regions [3]. The CCN plays a crucial role in emotion regulation and abnormalities in the associated regions can result in weakened cognitive control over negative affect [1, 3]. Cognitive control is implicated in a range of cognitive functions, such as working memory, attention span, and executive functions, loss of which can cause (increased) dysfunctional repetitive negative thinking, eliciting or aggravating depressive symptoms [18]. This specific vulnerability pathway has been supported by multiple MDD studies in adults, underscoring the importance of dedicated interventions targeting this crucial function [3, 8, 19]. Furthermore, in LLD the prevalence of impaired cognitive control functions is particularly high, which has also been associated with the reduced effectiveness of antidepressants [4, 42, 49]. An added treatment that specifically targets impaired cognitive control in older adults coping with depression may then be the preferred approach.

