### Aims and hypotheses

Our primary objective is to investigate whether the addition of a CCT program to ongoing LLD treatment (i.e., pharmacotherapy and/or psychotherapy) will help reduce depressive symptoms more so than a placebo training. Outcomes will be assessed 1 month post-training (T1) and during follow-up assessments at three (T2), six (T3) and 12 months (T4). We expect symptom reductions in the participants having received CCT to be greater than in the participants having completed the placebo training at all timepoints. Our second aim is to see whether CCT also exerts effects on other clinical measures including rumination (both trait and state), cognitive emotion regulation, working memory functioning (near and far transfer), inhibition, and quality of life. We expect that participants in the intervention group will show lower rumination, more adaptive cognitive emotion regulation, more improved working memory functioning, inhibition, and quality of life than the participants in the placebo group. Our third aim is to identify working mechanisms of CCT. We will examine whether improved working memory and reduced rumination mediate the effects of CCT on depressive symptoms, hypothesizing that improvements in depressive symptoms will follow improvement of working memory and reduction of rumination in the intervention group. Fourthly, we aim to study individual differences that could account for differences in the effect of CCT on symptom change, where we expect that baseline cognitive control, depression severity, and age will be moderating factors. Our fifth aim is to determine the cost-effectiveness of our add-on CCT, we will conduct a health-economic evaluation and budget-impact analysis, anticipating that CCT will reduce mental healthcare consumption during the follow-up period more so than placebo training. Finally, for our sixth aim, we will be assessing the acceptability and feasibility of the intervention by conducting qualitative interviews with subsamples of participants having received CCT, therapists involved in mental health care for older persons and other stakeholders to inform the further implementation of CCT as an add-on intervention next to existing treatments for LLD.

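### The main IDS-SR model adjusts only for the baseline outcome. That is valid, but adding age and one T0 cognition score the trial already collects would be a cheap, optional improvement

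*Protocol article*

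**What the plan says.** The Protocol article, under Evaluation of clinical outcomes, sets out a two-level mixed model over four time points. It contains condition, time and condition by time "as factors and the depended baseline measure as covariate". Age and baseline cognitive control appear in that section only as possible moderators. This matches Aims and hypotheses, where "we expect that baseline cognitive control, depression severity, and age will be moderating factors". The instrument for baseline cognitive control is not named.

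The Background gives a reason to think age and cognition matter for outcome under usual treatment. It says antidepressants work less well in older adults, "which is possibly related to age-related cognitive impairments". Of impaired cognitive control in late-life depression it adds, "which has also been associated with the reduced effectiveness of antidepressants". All participants receive ongoing depression treatment in addition to the study training.

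On cognition at baseline, the MoCA section says "The Montreal Cognitive Assessment will be used to screen for mild cognitive dysfunction at baseline (T0"). Table 1 schedules MoCA at T0 only, and also lists PASAT, RNG and Stroop at T0.

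The Sample size calculation makes no allowance for loss to follow-up and relies on mixed models or multiple imputation instead.

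**The concern.** Age and cognitive status are fixed before randomisation, are scheduled for every participant, and belong to constructs that the article itself ties to response under usual care. Leaving them out of the main model forgoes two possible benefits.

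The first is precision. Any variance in later IDS-SR that they explain beyond baseline IDS-SR stays in the error term, in a trial sized at 80% power with no reserve for drop-out.

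The second is protection against missing outcomes. The model's missing-at-random assumption holds given arm, time, baseline IDS-SR and the IDS-SR scores already observed. With baseline as a covariate, someone lost before T1 contributes no outcome row, so earlier scores cannot correct for that loss. The training adapts to performance and is described as eliciting frustration, whereas the placebo task does not load working memory. It is therefore conceivable that participants with lower cognitive scores are lost more often from the CCT arm. The remaining CCT group would then have a better prognosis than the placebo group, and the error would favour CCT.

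**Working it through.** **Inputs from the Sample size calculation.** The trial is planned "at α = 0.05 (2-tailed) and a power of (1-ß) = 0.80". The authors "opt for d = 0.45, corresponding to a medium-size effect". The correlation is "0.50 between baseline and first follow-up", and 0.50 again between follow-ups. Mean cluster size is 10, its coefficient of variation 0.475 and the ICC 0.05.

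**1. The plan's own figure.** For ANCOVA on the mean of k follow-ups, with outcome SD 1, the variance factor is (1 + (k − 1) × 0.50)/k − 0.50².
- k = 3: (1 + 1)/3 − 0.25 = 0.4167.
- n per arm = 2 × (1.96 + 0.8416)² × 0.4167 / 0.45² = 32.3, rounded up to 33. This reproduces the article.
- Design effect = 1 + ((0.475² + 1) × 10 − 1) × 0.05 = 1.563. Then 33 × 1.56 = 51.5, rounded up to 52 per arm and 104 in total. This also reproduces.
- The text speaks of four follow-ups but lists three. Four would give a factor of 0.375 and n = 30, so three is used here.
- At 33 per arm, SE = √(2 × 0.4167/33) = 0.159 and power = Φ(0.45/0.159 − 1.96) = 0.808.

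The stated power is therefore met with baseline IDS-SR as the only covariate.

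**2. Precision gain.** Let R² be the share of the residual variance of the follow-up mean that age and the cognition score explain. The article gives no value, so a range is assumed. The SE is multiplied by √(1 − R²).

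| Assumed R² | SE reduction | Power at 33 per arm |
|---|---|---|
| 0 | 0 | 0.808 |
| 0.02 | 1.0% | 0.816 |
| 0.05 | 2.5% | 0.828 |
| 0.10 | 5.1% | 0.847 |

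A joint partial correlation p with each single IDS-SR score corresponds to R² = p² × 0.75/0.4167. With p = 0.10 this is 0.018 (power 0.815). With p = 0.20 it is 0.072 (power 0.836). That is a gain of 0.7 to 2.8 points.

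**3. Loss of outcome data, one time point.** This simulation used 1,000,000 subjects, a true effect of −0.45, about 26% loss, and log-odds of loss of 0.7 per SD of cognition. All are assumptions.

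| Assumed slope of cognition on IDS-SR | Loss depends on cognition in | Baseline only | Cognition added |
|---|---|---|---|
| 0.1 | both arms equally | −0.450 | −0.450 |
| 0.2 | both arms equally | −0.447 | −0.448 |
| 0.3 | both arms equally | −0.445 | −0.446 |
| 0.1 | CCT only | −0.472 | −0.454 |
| 0.2 | CCT only | −0.485 | −0.450 |
| 0.3 | CCT only | −0.500 | −0.448 |

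With equal dependence the two models agree. With dependence in CCT only, the baseline-only estimate moves by about 0.02 to 0.05 SD towards CCT, and the covariate brings it back.

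**4. Loss of outcome data, longitudinal model.** This used four time points, all correlations 0.50, no true effect, monotone loss related to cognition in CCT only, and the same log-odds and slopes.
- Mostly early loss in CCT (24% by T1, 31% by T4): bias of 0.017 to 0.049 SD towards CCT.
- Mostly later loss in CCT (10% by T1, 26% by T4): bias of 0.009 to 0.032 SD towards CCT.
- With the cognition score in the model: about zero in both patterns.

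Using earlier IDS-SR scores thus reduces the shift when loss is late, but does not remove it.

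**The case against.** The case against is substantial. Baseline-adjusted analysis is a valid primary analysis, its covariate also carries the severity stratification factor, and the sample size was calculated for exactly this adjustment. Further covariates are often settled in a statistical analysis plan, which is not shown, and a journal article condenses. All of this stands, and it makes the point a suggestion. It does not dispose of the point, because the article states a covariate set instead of leaving it open.

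A reader might infer that the article links MoCA to treatment response. It does not. The links are to age, age-related cognitive impairment (worded as possible) and impaired cognitive control, and MoCA is presented as a screen. The age finding cited for the training concerns effect modification, which by itself promises no precision gain. Age and cognitive control will also enter the moderator models, which normally include their main effects, although those are not the main analysis.

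A reader might also infer that cognition-related drop-out biases the planned comparison. That requires loss of outcome data to depend on cognition differently in the two arms, and no section predicts this. Stopping the training is not the same as missing assessments: the Procedure section asks participants who miss sessions to complete all later assessments. Severe cognitive disability is an exclusion criterion, and multiple imputation, if chosen, could include these variables. A shift of 0.05 SD is about a third of the SE (0.05/0.159 = 0.31). Shifts up to 0.09 SD can be produced, but only with stronger assumptions (log-odds up to 1.0 per SD, coefficients up to 0.4) for which the documents give no support.

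Finally, T0 cognition is scheduled for everyone, but some baselines were done by telephone during the pandemic, so completeness is not assured.

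**Conclusion.** The planned model is sound and reaches its stated power. What remains is an opportunity: two baseline variables, already collected and prognostically plausible on the article's own account, could be added to the main model at almost no cost.

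The expected benefit is small: about 1 to 4 power points at an assumed R² of 2-10%, and removal of a shift of about 0.01-0.05 SD (2-11% of d = 0.45) only if loss of outcome data depends on cognition more in CCT than in placebo. Both ranges rest on assumed values. The documents support neither a claim that the baseline-only analysis is biased nor one that power is inadequate. If a statistical analysis plan already names these covariates, the point falls away.

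**What to change.** Before the data are analysed, add to Evaluation of clinical outcomes, or to the statistical analysis plan, that the IDS-SR model includes as fixed covariates, beside the baseline outcome, age (continuous, linear) and one named T0 cognition score (for example MoCA, linear). Keep the model with the baseline outcome only as a sensitivity analysis. If multiple imputation is used, put the same two variables in the imputation model.

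The cost is a sentence or two and two degrees of freedom, with no new data, visits or participants. A rule is needed for a cognition score missing at a telephone baseline. Filling in the overall mean is acceptable for precision under randomisation, but it does not remove drop-out bias for the participants whose score is unknown, and the plan should say so.
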